## Abstract

**Background:**

The diabetogenic action of statins remains a concern, particularly in patients at high risk for diabetes receiving intensive statin therapy. Despite the risk of diabetes with statin use being considered a potential class effect, recent studies have suggested that pitavastatin exerts neutral or favorable effects on diabetogenicity. However, no randomized trial has compared the long-term effects of pitavastatin with those of other statins on glycemic control in populations at high risk for diabetes. Hence, we aim to assess the long-term effects of pitavastatin in comparison with atorvastatin on glucose metabolism in patients with metabolic syndrome (MetS).

**Methods/design:**

The Long-term Effects of high-doSe pitavaStatin on Diabetogenicity in comparison with atorvastatin in patients with Metabolic syndrome (LESS-DM) trial is a prospective, randomized, open-label, active control clinical trial of patients with MetS. We plan to randomize 500 patients with MetS (1:1) to receive high-dose pitavastatin (4 mg) or atorvastatin (20 mg) daily for 24 months. The primary endpoint will be the change in hemoglobin A1c after statin treatment. Secondary endpoints will include the following: (1) changes in biochemical markers, including insulin, C-peptide, homeostasis model assessment of insulin resistance and insulin secretion, and adiponectin; (2) changes in imaging parameters, including carotid elasticity metrics and indices of cardiac function; and (3) the incidence of clinical events, including new-onset diabetes and cardiovascular disease.

**Discussion:**

In this trial, we will explore whether pitavastatin 4 mg does not disturb glucose metabolism in patients with MetS. It will also provide mechanistic information on statin type-dependent diabetogenic effects and surrogate data regarding vascular and cardiac changes achieved by intensive statin therapy.

**Trial registration:**

ClinicalTrials.gov, NCT02940366. Registered on 19 October 2016.

**Electronic supplementary material:**

The online version of this article (doi:10.1186/s13063-017-2229-4) contains supplementary material, which is available to authorized users.

## Background

Statins are powerful cholesterol-lowering drugs that can reduce morbidity and mortality. On the basis of these prognostic benefits, statins have been the mainstay of treatment for atherosclerotic cardiovascular disease (CVD) [1]. Furthermore, there is mounting evidence that statins can exert beneficial cardiovascular pleiotropic effects beyond their lipid-lowering actions [2]. However, there have been persistent concerns regarding the diabetogenic property of statins. In fact, several meta-analyses have demonstrated that statin treatment is associated with a 10–12% increased risk of new-onset diabetes mellitus (NOD) [3, 4]. Notably, this risk is further increased in patients treated with intensive statin regimens [5] and in subjects with preexisting risk factors for NOD [6]. In this regard, although the implications of statin-induced diabetes on the long-term outcomes are uncertain, statin-treated patients at high risk of developing NOD should be monitored regularly for changes in plasma glucose or hemoglobin A1c [7], especially when the patients are on intensive statin treatment. However, there are no randomized clinical trials addressing this problem.

An alternative strategy to mitigate the potential risk of statin-induced diabetes might include the use of less diabetogenic statins. Although whether the diabetogenic action of statins is a class effect remains controversial, recent studies have demonstrated that pitavastatin use might be associated with neutral, or even favorable, effects on glucose metabolism [8, 9]. However, an important limitation of these studies is their short follow-up duration. Furthermore, the underlying mechanism is poorly understood, although researchers in some studies have reported the possibility that adiponectin is associated with the effect of statins on the risk of NOD [10, 11].

Thus, the purpose of the present study, the Long-term Effects of high-doSe pitavaStatin on Diabetogenicity in comparison with atorvastatin in patients with Metabolic syndrome (LESS-DM) trial, is to investigate the long-term effect of pitavastatin on glucose metabolism in comparison with atorvastatin in patients with metabolic syndrome (MetS), a group at high risk for developing NOD. In this study, we also aim to evaluate changes in adiponectin to provide insight into the relevant mechanisms leading to statin-induced diabetes. Additionally, measurements of carotid elasticity and cardiac function by using carotid ultrasound and echocardiography, respectively, will be provided as surrogate imaging endpoints to compare the potential benefits of pitavastatin versus atorvastatin on the cardiovascular system before the clinical endpoint data can be obtained [12, 13].

## Methods/design

### Study rationale and objectives

This trial is a prospective, multicenter, randomized, open-label, active control study. The purpose of the study is to assess the effect of pitavastatin 4 mg daily versus atorvastatin 20 mg daily on changes in various parameters reflecting glucose metabolism in patients with MetS after 24 months of treatment. The time line of the study is illustrated in Fig. 1. The Standard Protocol Items: Recommendations for Interventional Trials (SPIRIT) checklist and figure are given in Additional file 1 and Fig. 2, respectively. The trial protocol is registered with ClinicalTrials.gov (NCT02940366).

**Fig. 1 Fig1:**
[figure not shown]
Study design of the Long-term Effects of high-doSe pitavaStatin on Diabetogenicity in comparison with atorvastatin in patients with Metabolic syndrome (LESS-DM) trial

**Fig. 2 Fig2:**
[figure not shown]
Standard Protocol Items: Recommendations for Interventional Trials (SPIRIT) figure

### Study participants

We will recruit from patients with MetS of both genders, aged 21 years or older, and who are candidates for statin therapy for prevention against CVD who visit outpatient clinics. These patients with MetS will be eligible only when they have no evidence of diabetes at baseline. Diabetes mellitus will be diagnosed as a random plasma glucose level ≥ 200 mg/dl along with classic symptoms of hyperglycemia, fasting plasma glucose level ≥ 126 mg/dl, 2-h postprandial plasma glucose level ≥ 200 mg/dl, and/or hemoglobin A1c ≥ 6.5%, or if a patient is taking medication for diabetes [14]. MetS will be defined according to the National Cholesterol Education Program Adult Treatment Panel III criteria [15]. The definition for anthropometric cutoff points of abdominal obesity will be based on the International Obesity Task Force criteria for the Asia-Pacific population [16]. The indication for statin therapy will be defined on the basis of the current guidelines [1]. Subjects fulfilling at least one of the following exclusion criteria will not be eligible for this study: (1) history of acute coronary syndrome or cerebrovascular disease in the past 2 months; (2) history of statin exposure within the past 1 month; (3) any anticipated change in statin regimen; (4) active malignancy; (5) cholestasis (serum total bilirubin > 3 mg/dl) or active liver disease (serum alanine transaminase > 200 IU/L); (6) chronic renal failure (serum creatinine > 2 mg/dl); (7) failure to obtain informed consent; (8) difficulty in completing follow-up; (9) concomitant use of medications affecting glucose metabolism, such as steroids and atypical antipsychotics; (10) known allergy to statins; and (11) any contraindication to statin therapy, including pregnancy/potential pregnancy, breastfeeding, cyclosporine use, myopathy, or genetic disorders.

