### Statistical analyses

The statistical analyses will be performed on both intention-to-treat and per-protocol bases. The intention-to-treat analyses will include all randomized participants who provide written informed consent, regardless of whether the study treatment is administered correctly. The per-protocol analyses will include all study participants who complete the trial with an adequate administration of the study drug (≥70% of the planned doses) and without any major protocol violations. Major protocol violations include inappropriate enrollment, the use of a prohibited concomitant medication, a violation of the dose or schedule of drug administration, or any other violation considered to be a major violation. The main analyses will be performed on an intention-to-treat basis.

The values will be expressed as the mean ± SD or median (IQR), as appropriate. Comparisons of continuous and categorical data will be made by Student’s *t* test and the chi-square test, respectively. The difference in changes between the groups will be analyzed using both Student’s *t* test and analysis of covariance to adjust for the baseline values. Two-sided *p* values < 0.05 will be considered statistically significant. All analyses will be performed using IBM SPSS version 22.0 software (IBM, Armonk, NY, USA).

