### Strengths and weaknesses

To date, there have been few head-to-head trials comparing the effects of different statins on glucose metabolism. Therefore, our study has an advantage in this respect because we will directly compare the effect of pitavastatin with that of atorvastatin, one of the most widely used statins clinically, on glucose metabolism and NOD. Another strength of this study is the provision of information regarding the impact of statins on adiponectin, which may give insight into the potential mechanisms underlying the difference in diabetogenic properties according to the statin type. This study also has an advantage in that it will include analyses of the effects of statin therapy on imaging surrogate markers, such as carotid elasticity metrics and echocardiographic parameters. On one hand, the results of these analyses will address the question whether the use of less-diabetogenic statin types has more beneficial effects on vascular and cardiac functions in patients at high risk for diabetes. On the other hand, the major limitation of our study is that the sample size is relatively small to detect differences in clinical outcomes, such as NOD or cardiovascular events, between the groups. To mitigate this limitation, we plan to use imaging surrogate endpoints, which may allow for a smaller sample size and a shorter study duration than clinical endpoints and thereby enable the assessment of the potential benefits of pitavastatin on cardiovascular outcomes. However, we should acknowledge that this approach based on imaging surrogate indicators cannot be fully applied to NOD. Another limitation is a lack of power to perform reliable subgroup analyses based on relevant variables. For example, given that age is a major risk factor for diabetes, subgroup analyses looking at narrower age ranges will provide additional valuable information on potential age group differences in the risk of statin-induced diabetes. Large clinical trials need to be conducted to determine which age group is the most susceptible for developing statin-induced diabetes or most benefits from the use of less-diabetogenic statins. With regard to gender, although there are no direct data on gender differences in the association between statin use and NOD, some previous studies suggested that diabetogenic potential of statins might be gender-specific by demonstrating that the baseline level of adiponectin and the effect of statins on adiponectin could be different between males and females [56, 57]. Further trials with adequate numbers of males and females are required to be able to answer the diabetogenic potential of statins based on gender differences. We should also acknowledge that the influence of previous statin use on the study endpoints cannot be completely excluded, even though we will exclude patients with a history of statin exposure within 1 month before enrollment and thus will perform stratified randomization according to the previous use of statins. Finally, patients receiving some antihypertensive agents with potential to affect glucose metabolism, such as thiazide-type diuretics, β-blockers, angiotensin-converting enzyme inhibitors, and angiotensin receptor blockers, which may be important covariates, can be included in our study [58]. If these covariates are not evenly distributed between study groups despite randomization, we will perform adjusted analysis in this randomized controlled trial to correct for the imbalances in covariates.

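### Exclusion criterion 9 bars drugs that affect glucose metabolism, while the Discussion admits antihypertensives credited with that potential; eligibility, the per-protocol terms and the covariate rule need reconciling

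*Protocol article*

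**What the plan says.** Three sections of the Protocol article bear on this.

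- **Study participants.** The list is binding: "Subjects fulfilling at least one of the following exclusion criteria will not be eligible for this study". Criterion 9 is "concomitant use of medications affecting glucose metabolism, such as steroids and atypical antipsychotics". The test is the drug's effect on glucose; the two named classes are examples.
- **Strengths and weaknesses.** The limitations discussion turns to "patients receiving some antihypertensive agents with potential to affect glucose metabolism, such as thiazide-type diuretics", and also names beta-blockers, ACE inhibitors and ARBs. It says of these drugs: "which may be important covariates, can be included in our study". On analysis it adds: "If these covariates are not evenly distributed between study groups despite randomization, we will perform adjusted analysis".
- **Statistical analyses.** The per-protocol set drops anyone with a major violation, and "Major protocol violations include inappropriate enrollment, the use of a prohibited concomitant medication". The same section gives priority to the other set: "The main analyses will be performed on an intention-to-treat basis". Changes are to be compared by t test and by analysis of covariance adjusted for the baseline value.

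**The concern.** Raised blood pressure is a component of metabolic syndrome, so users of these four classes are likely to be a visible part of the screened population. A screener who works from criterion 9 alone has grounds to turn them away. One who knows the limitations paragraph has grounds to enrol them. The trial is described as multicenter, so both readings could be in use at once, and the mix of patients randomized would then depend on who screened them.

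The same ambiguity can reach the per-protocol set. If criterion 9 is what gives meaning to wrongful enrolment or to a prohibited co-medication, a patient properly admitted under the limitations paragraph can later be classed as a major violator.

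There is also a weakness in the analysis rule. The article calls these drugs possibly important covariates, yet it adjusts for them only when the groups look unbalanced. The model for the primary endpoint would then depend on the observed data.

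**Working it through.** The plan gives no figure on this point, so the check is a comparison of the texts followed by what each reading implies.

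**Step 1: one patient, three sections.** Take a patient with metabolic syndrome on a thiazide at screening.

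| Section | Reading | Result |
|---|---|---|
| Study participants, criterion 9 | Drug acts on glucose; no exemption for antihypertensives | Ineligible |
| Strengths and weaknesses | Class named as admissible | Eligible |
| Statistical analyses | Depends on what counts as wrongly enrolled or prohibited | Violator if criterion 9 governs; not one if the limitations paragraph governs |

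The direct conflict is between the first two rows. The third does not contradict criterion 9; it carries the conflict into the per-protocol set.

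**Step 2: does the wording separate the two groups of drugs?** Criterion 9 speaks of drugs that affect glucose. The limitations paragraph speaks of "some antihypertensive agents with potential to affect glucose metabolism", which is slightly weaker. Criterion 9 sets no threshold, however, that would tell a screener when a potential effect becomes a disqualifying one.

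**Step 3: what happens to the per-protocol set?** Let *u* be the share of patients who would use such a drug and *r* the share of enrolled users later removed as violators. With 250 randomized per arm and the planned 10% dropout, at most 250 × 0.90 = 225 per arm complete. The per-protocol size is then at most 225 × (1 − *u* × *r*).

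- Criterion 9 applied literally at screening: users are never randomized, so *u* = 0 among those enrolled. Others are recruited up to the total of 500, and nothing is lost.
- Limitations paragraph applied throughout: users are eligible and stay, so *r* = 0. Nothing is lost.
- Mixed use, with enrolment under one text and removal under the other: the loss is *u* × *r*. The document gives neither quantity, so no value can be put on it.

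**Step 4: the main analysis.** The intention-to-treat set keeps every randomized participant who consented. Eligibility is settled before the web-based 1:1 allocation, so inconsistent screening changes who is studied but does not tilt the comparison between arms.

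**Step 5: the adjustment rule.** After randomization any imbalance in baseline drug use is due to chance. A covariate that predicts the outcome is worth including whether or not it is balanced, because it improves precision. Making its inclusion depend on an observed imbalance leaves the model open until the data are seen.

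**The case against.** The strongest reply is that the article settles the case itself. The limitations paragraph addresses these classes by name and plans for them in the analysis, so the specific statement can be read as limiting the general one. That makes the likely intent clear, and it stands. But the intent appears only in the Discussion; the operative criterion does not carry it.

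A second reply is that an article commonly leaves a list of prohibited medication to the full protocol. That also stands, and the absence of such a list is not the point here. The point is that the article states two rules that disagree.

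A reader might infer two stronger things. One is that the eligibility rules and the per-protocol definition contradict each other. They do not: read alone, they agree, and only the limitations paragraph departs from them. The other is that the per-protocol set would shrink badly and lose much of its power. The documents do not support this. It would need an assumed share of users, a reading of the 0.5% in the Sample size section as a standard deviation although the article calls it a variance, and the removal of every user after enrolment, which is the extreme case.

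It can also be said that a pre-specified covariate is an analysis preference and does not follow from an eligibility conflict. It is indeed a separate step, but the article's own imbalance-triggered rule for these drugs is the weaker method.

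**Conclusion.** The concern holds as a conflict between two stated rules, and it is worth correcting. It affects who is enrolled, and through the violation terms it may affect who stays in a secondary analysis set. It does not bias the main intention-to-treat comparison or reduce that analysis set. The extent of any per-protocol loss is unknown and cannot be derived from the document; it is zero if either text is applied consistently.

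The conclusion assumes that no unseen document already defines the disallowed drugs. If the full protocol does, the published wording still needs to be brought into line with it. The expectation that these drugs are common rests on blood pressure being part of the syndrome, not on any usage figure in the article.

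**What to change.** 1. Reconcile criterion 9, the limitations paragraph and the per-protocol definition through one stated list of drug classes that are allowed and not allowed. This review takes no position on which classes belong where.
2. Make criterion 9 refer to that list, and define both wrongful enrolment and prohibited co-medication in the per-protocol rules by reference to it. State whether the list applies at entry only or also to drugs started during the 24 months.
3. Replace the adjust-if-unbalanced rule with baseline use of any admitted glucose-active class as a pre-specified covariate in the analysis of covariance, alongside the baseline value.

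The cost is a short protocol clarification and a sentence in the analysis section. No new data are needed: the existing plan to adjust for these drugs already presupposes that their use is recorded. The Trial status section reports recruitment under way, so the clarification can still make later screening uniform. Patients already randomized stay in the intention-to-treat set.

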### Randomization

After the screening phase, randomization will be performed by using a web-based computerized program hosted at the Medical Research Collaborating Center of Seoul National University Hospital. With this program, eligible participants will be randomly allocated in a 1:1 ratio to receive either pitavastatin or atorvastatin. To ensure balance of the treatment groups with respect to gender, a randomization scheme will be performed separately within the stratum of gender. Stratified randomization according to previous use of statins will also be conducted to ensure even distribution of this factor between the study groups.

### Interventions

The trial will be conducted for 24 months. After randomization, the study participants will take pitavastatin 4 mg or atorvastatin 20 mg once daily. The prescription and administration of the study medications will be performed in an open-label manner. The dose of pitavastatin was set on the basis of a previous study in which researchers reported the effect of high-dose pitavastatin on glucose homeostasis [8]. Atorvastatin was chosen as the active control because it is the most commonly used statin and has been reported to result in an increase in insulin resistance and ambient glycemia [17]. The dose of atorvastatin was selected on the basis of previous experiments comparing these two statins [18, 19]. The investigators and clinical research coordinators will assess the drug compliance of the study participants, and those with < 70% compliance will be excluded from the per-protocol analysis. In addition to medical interventions, lifestyle modifications will be encouraged as background therapy in this study. On the basis of previous studies, the patients’ smoking status, alcohol consumption, diet, and level of physical activity are considered major modifiable lifestyle factors [20, 21]. Thus, the patients will be instructed and encouraged to adhere to healthy lifestyles, including not smoking, no excessive alcohol consumption, low-risk diets, and being physically active.

### Measurements

Data on the patients’ medical history, physical examination findings, vital signs, anthropometric measures, blood biochemical tests, and imaging parameters will be collected by trained staff at our institution. Weight and height will be measured by trained nurses, and body mass index will be calculated as the weight in kilograms divided by height in meters squared. Body composition will be assessed using a multifrequency bioimpedance analyzer (InBody 720; InBody, Seoul, Korea) [22].

The primary endpoint of this study is the change in hemoglobin A1c after 24 months of statin treatment. The secondary endpoints include changes in other laboratory variables, such as insulin, C-peptide, the insulin resistance index of the homeostasis model assessment, the insulin secretory ability index of the homeostasis model assessment, lipid profiles (including total cholesterol, triglycerides, high-density lipoprotein cholesterol, and low-density lipoprotein cholesterol), adiponectin, C-reactive peptide, and troponin I, after 24 months of statin treatment. Carotid ultrasound and echocardiography will be performed at baseline and after 12 and 24 months of therapy to obtain data on carotid elasticity and cardiac function, respectively. Specifically, the carotid elasticity metrics, including strain, stiffness, and distensibility by the B-mode and speckle-tracking methods, will be measured as described previously [23]. The imaging parameters of cardiac function to be measured include the left ventricular global longitudinal strain by speckle-tracking echocardiography as well as traditional indices derived from two-dimensional, Doppler, and tissue Doppler echocardiography [24]. Additional file 2 provides a detailed description of the methods that will be used to measure the carotid ultrasound and echocardiographic parameters.

In addition, the incidences of NOD and CVD, including coronary heart disease (angina, myocardial infarction, cardiac revascularization, or coronary death), stroke (fatal or nonfatal ischemic stroke), heart failure, arrhythmia, peripheral vascular disease, and venous thromboembolism, will be assessed during the follow-up of this trial. Follow-up of these clinical events will be performed by means of in-office visits, medical record review, and telephone contact. Specifically, trained research personnel who are unaware of the study group assignments will review all medical records and will also conduct telephone interviews if needed to monitor the development of clinical events. The schedule for the assessments is summarized in Table 1.

**Table 1 Tab1:** Schedule of study assessments

	V1 (Baseline)	V2 (6 months)	V3 (12 months)	V4 (18 months)	V5 (24 months)
Informed consent	√				
Medical history	√	√	√	√	√
Physical examination	√	√	√	√	√
Vital signs	√	√	√	√	√
Anthropometric measures	√		√		√
Blood tests					
Complete blood count	√				√
Routine blood chemistry	√		√		√
Lipid profile	√		√		√
Fasting plasma glucose	√		√		√
Hemoglobin A1c	√		√		√
Insulin	√		√		√
C-peptide	√		√		√
HOMA-R	√		√		√
HOMA-β	√		√		√
Adiponectin	√		√		√
High-sensitivity CRP	√				√
Cardiac troponin I	√				√
Creatine kinase	√		√		√
Carotid ultrasound					
Strain by B-mode	√		√		√
Stiffness by B-mode	√		√		√
Distensibility by B-mode	√		√		√
Strain by speckle tracking	√		√		√
Stiffness by speckle tracking	√		√		√
Echocardiography					
2D measurements	√		√		√
M-mode parameters	√		√		√
Doppler parameters	√		√		√
Tissue Doppler parameters	√		√		√
2D speckle-tracking analysis	√		√		√
Clinical events	√	√	√	√	√

*Abbreviations: HOMA-R* Insulin resistance index of homeostasis model assessment, *HOMA-β* Secretory ability of homeostasis model assessment, *CRP* C-reactive protein, *2D* Two-dimensional

